### Study Settings and Participants

Our proposed study is anchored on the intervention for Sustained Testing and Retention (iSTAR) Among HIV-infected Patients, an ongoing NIH-funded study in Benue state, north-central Nigeria (NIH grant No. R01HD087994-01). The iSTAR is based on the HBI, our previous work that demonstrated that pregnant women and their male partners can be effectively screened in the community for HIV, SCD, and HBV (NIH grant No. R01HD075050) [22,26]. In 2012, Benue state was projected to have a population of 4,768,877, with 49.6% females and a fertility rate of 4.9% [33]. According to the 2013 Nigeria Demographic and Health Survey, about 70% of the female population had attained less than a secondary education with a literacy rate of 52.8%. Most (74.8%) were farmers residing in rural areas [34]. Preliminary data from our ongoing study demonstrates that in Benue state, prevalence rates of HIV, HBV, and SCD among pregnant women is 7.8%, 11.13%, and 19.1%, respectively.

### Participant Recruitment—Healthy Beginning Initiative

A detailed description of the baby shower program has been published previously [22]. The HBI was designed and initially tested in southeastern Nigeria as a sustainable, culturally adapted, community-driven program delivered by community health advisors to identify pregnant women, implement health interventions, and support linkage to health services for women and their families. Briefly, it has three main platforms: (1) prayer sessions during church services are used to identify pregnant women, allowing for multiple opportunities to offer health interventions; (2) church-organized baby showers are used to implement interventions that include health education and on-site integrated laboratory screening, including HIV testing; and (3) baby receptions held 6-8 weeks after birth following infant baptism to enhance postdelivery follow-up and increase early infant diagnosis [22,23]. The United States President's Emergency Plan for AIDS Relief (PEPFAR)-supported implementing partner in Benue state, Caritas Nigeria, has scaled up this approach in the priority areas where the proposed study will be conducted.

### Study Procedure

#### Overview

We will leverage existing technology to develop a mobile health platform that integrates a database, smart card technology, and a mobile phone-based app to make results available at the point of care without the need for Internet connection. Subsequently, we will recruit 300 women who attend church-organized baby shower programs in the four priority local government areas and who consent to participate in the study.

#### Inclusion and Exclusion Criteria

Participants are eligible if they have a positive test result for (1) HIV, (2) hepatitis B surface antigen, and/or (3) sickle cell trait or disease, as defined by heterozygosity (AS) or homozygosity (SS), respectively, for the S variant of hemoglobin β-subunit; and (4) are residing in the local government areas where the four health facilities are situated. Those who decline to have their test results uploaded on the secure Web-based database will be excluded.

Data from the ongoing HBI will be reviewed by study staff to determine eligible participants. Trained research assistants will approach each participant independently to inform them about the study. HBI participants who consent to enroll in the study will have data collected from their community screening session stored in a secure, Web-based database. The stored data will be encrypted into a Quick Response (QR) code embedded on a *smart card* with a unique identification number printed on the outside of the card. There will be no names or any other identifiers. The smart card will be offered to each participant. The research assistants will administer a questionnaire to each participant to collect information on acceptability of the smart card. Each participant will be asked to present the smart card at prenatal visits and delivery at the selected health care facility. At the health care facility, we will identify dedicated delivery room staff that will be trained to scan the smart card and read its contents using the mobile phone app without the need for Internet connection. Mobile phones will be provided to each facility to use for the duration of the study. When a participant presents at delivery without the card, information can still be obtained from the secure, Web-based database and confirmed using the participant’s name, date of birth, and mobile phone number.

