### Our Proposal and Objectives

We propose to develop an integrated mobile health platform that is able to collect data in the community, integrate collected data into a smart card, and read the smart card using a mobile phone-based app without the need for Internet access.

Our primary objective is to determine the feasibility of developing this integrated mobile health platform. Our secondary objectives are to (1) determine the acceptability of the smart card among pregnant women and (2) determine the usability of the smart cards by the pregnant women and health facilities.

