### Study Outcomes and Analysis

#### Acceptability

We will assess the proportion of pregnant women who are willing to allow health care workers to retrieve information from their card.

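### Acceptability is collected by the staff group that introduces the study to the women, so the stated-willingness proportion is at risk of upward courtesy bias of unknown size

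*Protocol article*

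**What the plan says.** Acceptability is a secondary objective: to "determine the acceptability of the smart card among pregnant women" (Our Proposal and Objectives). The measure is in the Acceptability section: "We will assess the proportion of pregnant women who are willing to allow health care workers to retrieve information from their card".

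The procedure is in Inclusion and Exclusion Criteria, in this order:

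- Recruitment: "Trained research assistants will approach each participant independently to inform them about the study".
- Selection: "Those who decline to have their test results uploaded on the secure Web-based database will be excluded".
- Card: "The smart card will be offered to each participant".
- Measurement: "The research assistants will administer a questionnaire to each participant to collect information on acceptability of the smart card".

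The planned sample is 300 women (Overview). No expected willingness, precision target or acceptability threshold is given.

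Two other parts bear on the point. Theoretical Framework assigns feasibility and acceptability to Reach and Effectiveness, and the Reach and Effectiveness section measures the percentage of women who use the card at delivery. Assessing Usability by Participants plans interviews and focus groups on barriers to card use.

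**The concern.** The team that presents the study also asks whether its central product is acceptable. Every participant has a positive result for HIV, hepatitis B or sickle cell trait or disease, and was found through a church-organized program. The question is whether she will let health workers read that result. In that setting a reluctant woman may find yes the easier answer to give to the enrolling team.

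What is at stake is the one number that the Acceptability section defines. If some unwilling women answer yes, the proportion overstates acceptability, and its confidence interval gives no sign of it.

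**Working it through.** **The text, step by step.** The article names trained research assistants as the people who inform the women. A few sentences later it gives the questionnaire to the research assistants, with a definite article that points back to the same staff group. It describes no separate interviewer and no confidential answer.

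**No figure to reproduce.** The article states no proportion, precision or power for this endpoint, so what follows is illustration only.

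**Inputs.**
- n = 300, from Overview, taking all enrolled women as respondents.
- p, true willingness among respondents: assumed, 60% to 90%.
- c, share of unwilling women who say yes out of courtesy: assumed, 10%, 25% or 50%.

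**Formulas.**
- Expected observed proportion = p + c(1 − p)
- Bias = c(1 − p)
- 95% half-width at p = 1.96 × √(p(1 − p)/300)
- Courtesy share at which bias equals the half-width = half-width/(1 − p)

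**Worked case, p = 80%.**
- c = 10%: 0.80 + 0.10 × 0.20 = 0.82, bias 2 points
- c = 25%: 0.80 + 0.25 × 0.20 = 0.85, bias 5 points
- c = 50%: 0.80 + 0.50 × 0.20 = 0.90, bias 10 points
- Half-width: 1.96 × √(0.80 × 0.20/300) = 0.045, or 4.5 points
- Bias equals half-width at 0.0453/0.20 = 0.23

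**Range over the assumptions.**

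| True willingness p | Observed at c = 10 / 25 / 50% | Bias (points) | 95% half-width (points) | c at which bias = half-width |
|---|---|---|---|---|
| 60% | 64 / 70 / 80% | 4 / 10 / 20 | 5.5 | 14% |
| 70% | 73 / 77.5 / 85% | 3 / 7.5 / 15 | 5.2 | 17% |
| 80% | 82 / 85 / 90% | 2 / 5 / 10 | 4.5 | 23% |
| 90% | 91 / 92.5 / 95% | 1 / 2.5 / 5 | 3.4 | 34% |

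With c = 0 there is no bias. The bias formula contains no n, so recruiting more women narrows the interval and leaves the bias as it is.

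**Selection before the question.** Women who decline consent or data upload are out before willingness is asked. The proportion therefore describes women who have already agreed to something close to what they are asked. This pushes the figure above that for all eligible women, separately from any courtesy effect.

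**The case against.** The strongest case against has five parts.

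*The text does not say that one individual does both tasks.* This stands. It names a staff category. Nor does it say that the answer is spoken or a simple yes or no; that an interviewer asks the questions is a fair reading of the word administer, and the 52.8% literacy rate in Study Settings and Participants is a good reason for working that way. A reader might also infer that the woman is asked moments after she enrols. The documents do not support that: the abstract's Results report the 300 women as recruited with the card offer still ahead, and the questionnaire is described after the card offer, with no time given. The risk needs only that the enrolling team asks, but a long gap could weaken it.

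*The direction is not certain.* A reader might conclude that courtesy answers do inflate the result, and can only inflate it. Nothing in the documents shows either. The Background lists confidentiality and HIV-related stigma as barriers, and these could make a willing woman guarded. At p = 80% and c = 25%, the 5-point rise would be cancelled if 0.05/0.80 = 6.25% of willing women said no. Upward is the likelier direction, but it is a judgement.

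*The size depends on the inputs.* This stands. Because refusers of upload are excluded first, willingness among respondents may be high. At an assumed 95%, courtesy shares of 25% and 50% add 0.05 × 0.25 = 1.25 and 0.05 × 0.50 = 2.5 points, against a half-width of 1.96 × √(0.95 × 0.05/300) = 2.5 points.

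*Acceptability does not rest on this proportion alone.* This is true in part. Card use at delivery, taken from records, and the qualitative work on barriers add evidence. Neither corrects the proportion, and card use also depends on the woman attending and bringing the card.

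*A journal article condenses, and the full protocol may hold the safeguard.* This would answer a complaint about omitted detail. Here the article states who administers the questionnaire, and the point concerns that stated choice. If a safeguard exists elsewhere, one sentence in the article would settle the matter.

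**Conclusion.** The point holds as a risk of bias. The staff group that informs women about the study also administers the acceptability questionnaire, the measure is stated willingness, and no safeguard is described. The likely direction is upward and the size is unknown. Under the assumed inputs the bias runs from 1 point (p = 90%, c = 10%) to 20 points (p = 60%, c = 50%). It passes the sampling half-width once roughly 14% to 34% of unwilling women say yes, depending on true willingness between 60% and 90%.

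The consequence is limited. Acceptability is a secondary objective, and the article sets no threshold or comparison that a few points would tip. The change is worth making because it is cheap and, on the timing given in the abstract, still possible.

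**What to change.** In Inclusion and Exclusion Criteria, state that the willingness item is answered confidentially. One workable form is a picture-symbol slip, suited to the stated literacy, that carries only the card's ID number and goes into a sealed box. The ID number keeps the link to the woman's condition, and the assistant does not see her answer. The rest of the questionnaire can stay with the assistants.

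As an alternative, where feasible within the same site team, the item can be asked by an assistant who did not recruit that woman. This is weaker, because study staff still ask. Exchanging assistants between local government areas should not be the main remedy: it adds travel and widens the circle of people who know a woman's test status.

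In reporting, place the willingness proportion beside recorded card use at delivery (Reach and Effectiveness), and describe its denominator as enrolled women who had already agreed to data upload.

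Cost: slightly more handling of slips, or some scheduling within the site team. No extra staff are needed.

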### Study Outcomes and Analysis

#### Acceptability

We will assess the proportion of pregnant women who are willing to allow health care workers to retrieve information from their card.

#### Reach and Effectiveness

Reach will be calculated as the number of enrolled pregnant women relative to the number of eligible pregnant women in the study catchment area. The effectiveness will be determined by assessing the impact of the mHealth platform on key outcomes, such as screening for HIV, HBV, and sickle cell genotype and health care utilizations for follow-up visits. This will be measured by calculating the percentage of pregnant women that use the smart cards at the point of delivery, thus reducing the need for repeat testing and reducing missed opportunities for reduction of perinatal transmission of HIV and HBV and deaths among children with SCD. The reach and effectiveness of the mHealth platform will be captured through patient records and recruitment assessments.

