### Preliminary Studies

The HBI is a community-driven, congregation-based intervention that provides health education and on-site integrated laboratory testing—HIV plus hepatitis B and sickle cell genotype—during church-organized baby showers. In 2014, we demonstrated that the HBI was feasible, acceptable, and effective in increasing uptake of HIV, hepatitis B, and sickle cell genotype testing among pregnant women and identification of infected/affected women in southeast Nigeria (National Institutes of Health [NIH] grant No. R01HD075050) [22,26]. We subsequently demonstrated that when maternal results are made available at the point of delivery, clinicians were more likely to initiate antiretroviral prophylaxis for the HIV-exposed infant and give the first dose of hepatitis B vaccine to an infant born to a mother with hepatitis B surface antigen within 24 hours. Clinicians were also more likely to screen infants for SCD, who were born to mothers with sickle cell trait, to allow for early institution of penicillin prophylaxis and appropriate immunization. Until recently, the use of information technology to make prenatal data available at the point of delivery has been limited to high-income countries due to poor infrastructure in developing countries. Fortunately, the unprecedented spread of mobile technology has made it possible to develop mHealth platforms that can be used to provide similar services to hard-to-reach communities in resource-limited settings [23,27]. This has led to improved quality of care and decreased rate of unnecessary testing, and has allowed for early institution of evidence-based interventions that improve birth outcome [28-31].

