### Theoretical Framework

Glasgow’s Reach, Effectiveness, Adoption, Implementation, and Maintenance (RE-AIM) framework is used as a guide to assess the implementation of the mHealth platform. The RE-AIM framework offers a comprehensive approach to considering five dimensions important for evaluating the potential public health impact of an intervention [32]. The model includes the following: (1) *Reach*, the percent and representativeness of individuals willing to participate; (2) *Effectiveness*, the impact of the intervention on targeted outcomes and quality of life; (3) *Adoption*, the percent and representativeness of settings and intervention staff that agree to deliver a program; (4) *Implementation*, the consistency and skill with which various program elements are delivered by various staff; and (5) *Maintenance*, the extent to which individual participants maintain behavior change long term and, at the setting level, the degree to which the program is sustained over time within the organizations delivering it [32]. *Reach* and *Effectiveness* will assess feasibility and acceptability, while *Adoption*, *Implementation*, and *Maintenance* will assess usability and sustainability of the mHealth platform.

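### Effectiveness is announced as impact on outcomes but measured as card use at delivery, which is uptake and cannot show fewer repeat tests or missed opportunities

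*Protocol article*

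**What the plan says.** All places are in the protocol article.

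- **Reach and Effectiveness, the construct:** "The effectiveness will be determined by assessing the impact of the mHealth platform on key outcomes, such as screening for HIV, HBV, and sickle cell". Follow-up utilization is the other example given.
- **Same section, the measure:** "This will be measured by calculating the percentage of pregnant women that use the smart cards at the point of delivery".
- **Same sentence, the inferred benefit:** "thus reducing the need for repeat testing and reducing missed opportunities for reduction of perinatal transmission of HIV and HBV and deaths among children with". (The children meant have sickle cell disease.) The named data sources are patient records and recruitment assessments.
- **Theoretical Framework:** Effectiveness means "the impact of the intervention on targeted outcomes and quality of life". The section ends by assigning Reach and Effectiveness to the assessment of feasibility and acceptability.
- **Inclusion and Exclusion Criteria, entry rule:** "Participants are eligible if they have a positive test result for (1) HIV, (2) hepatitis B surface antigen, and/or (3) sickle cell trait or disease". The card is loaded with earlier results: "HBI participants who consent to enroll in the study will have data collected from their community screening session stored in a secure, Web-based database". Every participant is offered a card. If a woman arrives at delivery without it, staff can still look up her results in the Web database.
- **Preliminary Studies:** the community session tests for HIV, hepatitis B and sickle cell genotype together. When results were available at delivery, clinicians were more likely to take three infant actions: start antiretroviral prophylaxis, "give the first dose of hepatitis B vaccine to an infant born to a mother with hepatitis B surface antigen within 24 hours", and screen infants of mothers with sickle cell trait for SCD.

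**The concern.** The measure and the construct are different things. The percentage of women who present a card describes exposure to the intervention. Impact is what changes because of that exposure. Reach and Effectiveness joins the two with the word thus, so the benefit is assumed to follow from use.

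Followed as written, the plan would report high effectiveness whenever many women brought their cards, even if every one of them was retested and infant care was unchanged. The Discussion treats the link from results at delivery to better care as not yet well shown in many such settings. The measure therefore takes for granted the answer to a question that the article itself calls open.

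The first outcome named, screening, is also badly placed. If it means maternal screening, it took place before the card existed.

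**Working it through.** The article states no power, effect size or target for this outcome, so there is no figure to reproduce. The check sets sections against each other and adds one illustration.

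**1. Measure against definition.** Theoretical Framework defines Effectiveness by effect on targeted outcomes and quality of life. Reach and Effectiveness measures the share of women using the card. Card use is neither a targeted outcome nor quality of life. No measure of repeat tests or infant actions is given there.

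**2. Card use against availability of results.** The earlier evidence in Preliminary Studies concerns results being available at delivery. Under Inclusion and Exclusion Criteria, results can also be reached through the database without the card. Card use is therefore an imperfect proxy even for availability, and that evidence does not validate it as a measure of effect.

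**3. Can maternal screening respond?** Eligibility needs at least one positive result, so at least one test is complete in every participant at entry. Preliminary Studies describes the session as integrated testing for all three conditions, which implies that the other two are normally complete as well. The card only carries those results, so it cannot alter that screening.

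**4. How well is uptake estimated?** Input: n = 300 (Study Procedure, Overview). Half-width of the 95% CI = 1.96 × √(p(1 − p)/300).

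- p = 50%: 1.96 × √(0.25/300) = 5.7 points
- p = 70%: 1.96 × √(0.21/300) = 5.2 points
- p = 90%: 1.96 × √(0.09/300) = 3.4 points

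Card use itself is well estimated.

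**5. Does uptake identify the benefit?** Let u be card use, r0 the repeat-test rate without the card and r1 the rate among users. The overall rate is u·r1 + (1 − u)·r0, so the reduction is u·(r0 − r1). The article gives neither r0 nor r1; the values below are assumptions. Take u = 0.70 and r0 = 0.60:

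| r1 | Reduction | Effectiveness as the plan reports it |
|---|---|---|
| 0.60 | 0.70 × 0.00 = 0 points | 70% |
| 0.30 | 0.70 × 0.30 = 21 points | 70% |
| 0.00 | 0.70 × 0.60 = 42 points | 70% |

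The same reported result fits no benefit and a large one.

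**The case against.** The strongest defence is that this is a single-group feasibility study. Theoretical Framework assigns Reach and Effectiveness to feasibility and acceptability, and no objective claims a clinical effect. The abstract's conclusions say only that findings could offer a new approach. Card use at delivery is a sensible feasibility measure, and a condensed article may leave further variables to the full protocol.

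Much of this stands. Card use should be kept, and neither the primary nor the secondary objectives fail because of this point. It does not rescue the wording: the article does not leave the measure open. It names one, calls it the measure of impact, and attaches less repeat testing and fewer missed opportunities to it.

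Four stronger readings are tempting, and the documents do not support them.

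- **That screening is fixed at 100% for all three conditions.** The eligibility wording is and/or, so it guarantees only one completed test. Completeness for all three rests on the description of integrated testing. Screening is also given only as an example and might mean infant screening, although the section does not say so. The other named outcome, follow-up utilization, is not fixed at entry.
- **That the study plans to assess SCD deaths and is too small to do so.** The clause concerns missed opportunities to reduce deaths. No count of deaths is proposed.
- **That the lack of a comparator is an error.** In a single-group feasibility study it is not. It only limits what may be called impact.
- **That overlapping programmes confound the estimate.** The article describes the anchor study's outcomes no further than its title, and no planned estimate compares groups.

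**Conclusion.** The point holds as a mismatch between construct and measure. What is called Effectiveness is card uptake. It contradicts the article's own definition, and the claimed reductions are asserted without being measured. Maternal screening cannot serve as an outcome of the card.

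The size is qualitative: uptake would be known to within about 6 points, while any benefit would remain unidentified (0 to 42 points in the illustration, which rests on assumed repeat-test rates). The conclusion itself rests on the text and not on those rates. The claim that all three maternal tests are complete at entry does depend on the integrated session having been carried out as described.

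Severity is moderate: the primary objective is feasibility, and card use remains valid for that. The risk is a published effectiveness claim that the data cannot support.

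**What to change.** In Reach and Effectiveness:

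1. Report the percentage using the card at delivery, among all enrolled women, as card uptake, a feasibility measure. Do not file it under Implementation, which Assessing Usability by Health Care Workers already defines as fidelity.
2. Delete maternal screening as an effectiveness outcome, or state that infant screening is meant.
3. Drop the impact wording and the clause on reduced repeat testing, missed opportunities and SCD deaths, or mark them as hypotheses that this single-group study does not test.
4. If an Effectiveness measure is kept, take it from the patient records already named as a source: the proportion retested at delivery for a result already on the card, and the documented infant actions listed in Preliminary Studies. Report by maternal condition, with all enrolled women with that condition as the denominator, whether or not the card was shown. Show women without an accessible delivery record separately. Give 95% CIs and describe the results as uncontrolled.

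Comparison with facility records from before roll-out is optional, and only where they exist. The Results section describes the sites' HIV services; nothing shows that they hold earlier hepatitis B or sickle cell records.

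Step 4 would give usable descriptive precision. Assume independent conditions, enrolment in proportion to the Benue prevalences in Study Settings and Participants (7.8%, 11.13%, 19.1%, the last read as trait or disease), and complete records. The eligible share is 1 − 0.922 × 0.8887 × 0.809 = 0.337. Expected numbers are 300 × 0.078/0.337 = 69 with HIV, 300 × 0.1113/0.337 = 99 with hepatitis B and 300 × 0.191/0.337 = 170 with sickle cell trait or disease, with overlap. At a proportion of 50%, the half-widths 1.96 × √(0.25/n) are about 11.8, 9.8 and 7.5 points.

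The cost is a wording change and a less favourable effectiveness claim. Step 4 adds a few fields from patient records, and access to them must be confirmed. No clinical procedure changes.
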